Seventy two (60 vaccine and 12 placebo) volunteers will be enrolled and assigned to one of six cohorts as outlined in **Tables 1 & 2**. All vaccines will contain the same amount of Montanide® ISA51. As with other recombinant protein vaccines, hypersensitivity reactions would be expected to occur within the first 24 hours after receipt of the vaccine, and other severe local or systemic reactions within 72 hours, and possibly up to 3 weeks post-vaccination. The vaccinations will be staggered within one dose cohort such that four volunteers will be vaccinated three weeks prior to the remaining 8 volunteers. Therefore, 35 days of safety data will be available for the first 4 vaccinees and 21 days of safety data for the remaining 8 volunteers post-vaccination from the lower dose cohort for review by the Safety Monitoring Committee (SMC) prior to dose escalation. Dose escalation will not occur less than 3 weeks from the remaining 8 volunteers in the lower dose cohort being vaccinated. The trial will not proceed to the next dose cohort if, in the clinical judgment of the SMC, the next higher dose would pose an unacceptable safety risk to the volunteers. The PpPfs25 and ScPvs25 formulations will be considered individually by the SMC prior to dose escalation. The following table represents the earliest projected vaccination dates based on the safety intervals described above. These represent only tentative dates and may change based on recommendations of the Safety Monitoring Committee and/or the study staff.

Tables 1 and 2: Vaccination Schedule

| **PpPfs25/ISA51 Vaccine Dose Escalation Schedule** | | | | |  | **ScPvs25/ISA51 Vaccine Dose Escalation Schedule** | | | | |
| --- | --- | --- | --- | --- | --- | --- | --- | --- | --- | --- |
|  |  | Cohort A1: (n=12) | Cohort B1: (n=12) | Cohort C1: (n=12) |  |  |  | Cohort A2: (n=12) | Cohort B2: (n=12) | Cohort C2: (n=12) |
| Date | Week | 5µg | 20µg | 80µg |  | Date | Week | 5µg | 20µg | 80µg |
| 5/23/05 | 0 | **Vax 1 (n=4)** |  |  |  | 6/13/05 |  |  |  |  |
| 5/30/05 | 1 |  |  |  |  | 7/11/05 | 0 | **Vax 1 (n=4** |  |  |
| 6/6/05 | 2 | **Vax 1 (n=5)** |  |  |  | 7/18/05 | 1 |  |  |  |
| 6/13/05 | 3 |  |  |  |  | 7/25/05 | 2 |  |  |  |
| 6/20/05 | 4 | **Vax 1 (n=3)** |  |  |  | 8/1/05 | 3 | **Vax 1 (n=4)** |  |  |
| 8/22/05 |  |  |  |  |  | 8/22/05 |  | **Vax 1 (n=4)** |  |  |
| 9/26/05 | 18 | **Vax 2 (n=4)** |  |  |  | 9/26/05 | 11 |  | **Vax 1 (n=4** |  |
| 10/3/05 | 19 |  |  |  |  | 10/3/05 | 12 |  |  |  |

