3. Collect Days 14 – 20 diary card.

Study Day 30 +/- 7(1 month after first vaccination)

1. Perform basic history and physical exam (including injection site), emphasizing examination of any acute complaints.
2. Record vital signs.
3. Obtain approximately 5 mL of blood for antibody ELISA.

Study Day 60 +/- 7 (2 months after first vaccination)

1. Perform basic history and physical exam (including injection site), emphasizing examination of any acute complaints.
2. Record vital signs.
3. Obtain approximately 35 mL of blood for hematology biochemistry, antibody ELISA & membrane feeding assay.

Study Day 90 +/- 7 (3 months after first vaccination)

1. Perform basic history and physical exam (including injection site), emphasizing examination of any acute complaints.
2. Record vital signs.
3. Obtain approximately 5 mL of blood for antibody ELISA.

Study Day 120 +/- 7 (Day of Second Vaccination)

1. Perform basic history and physical exam (including injection site), emphasizing examination of any acute complaints.
2. Obtain approximately 35 mL of blood for hematology, biochemistry, antibody ELISA, and membrane feeding assay
3. For females, obtain a urine sample for -hCG testing. Ensure that test is negative before vaccinating; a positive test will exclude the volunteer from the trial.
4. Record vital signs (blood pressure, temperature, heart rate and respiratory rate).
5. Administer the vaccine.
6. Observe for at least 30 minutes after vaccination to evaluate for immediate adverse reactions.
7. Education by study staff during 30-minute post-immunization wait period describing proper use of digital thermometers, injection-site reaction measurement tools and patient diaries. Study staff will also discuss signs and symptoms of potential AEs.
8. Distribute Days 0-6 diary card.

Study Day 121 (1 day after Second Vaccination)

1. Perform basic history and physical exam (including injection site), emphasizing examination of any acute complaints.
2. Record vital signs.

Study Day 123 (3 days after Second Vaccination)

1. Perform basic history and physical exam (including injection site), emphasizing examination of any acute complaints.
2. Record vital signs.
3. Obtain approximately 10 mL of blood for hematology and biochemistry tests.

Study Day 127 +/- 1 (7 days after Second Vaccination)

1. Perform basic history and physical exam (including injection site), emphasizing examination of any acute complaints.
2. Record vital signs.
3. Collect Days 0-6 diary card.

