### Safety Monitoring Committee

MVDB, in consultation with RCHSPB, will select three independent monitors to advise RCHSPB and the study investigators on the trial. These individuals will be independent of MVDB and the clinical trial site. The SMC’s primary responsibility will be to monitor volunteer safety. The Principal Investigator is responsible for ensuring that the SMC is aware of all new safety information. The SMC will periodically review individual and cumulative volunteer data on safety and enrollment when making recommendations regarding the safe continuation of the study. If no stopping criteria are met (**Section 7.5**), dose escalation will proceed with approval from the SMC. The SMC will review cumulative safety data for evidence of study-related AEs, adherence to the protocol, and factors that may affect outcome or study data such as protocol violations and losses to follow-up. Because of the staggered start for each dose group, the SMC will meet after the second part of the dose group (n=8) has been evaluated for at least 14 days post-vaccination; such that 35 days of safety data will have accumulated for the first 4 vaccinees, and 21 days of safety data will have accumulated for the remaining 8 vaccinees. The SMC will review the cumulative safety data following the first vaccination of the lower dose group to approve dose escalation, as well as following the second vaccination prior to dose escalation, and whenever the need should arise, to review study conduct and cumulative safety data, as well as at the discretion of the SMC and/or study investigators.

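### Section 7.4.2 lets the SMC meet on escalation when the last 8 volunteers have 14 days of data, against the 21 days it is said to review, and the 35/21-day package does not fit the 3-week stagger

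*Protocol*

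**What the plan says.** Section 3.1 (Overall Design) staggers each cohort of 12: "four volunteers will be vaccinated three weeks prior to the remaining 8 volunteers". It describes the package the SMC is to have before escalation: "35 days of safety data will be available for the first 4 vaccinees and 21 days of safety data for the remaining 8 volunteers". It then sets a floor: "Dose escalation will not occur less than 3 weeks from the remaining 8 volunteers in the lower dose cohort being vaccinated". The footnote to Tables 1 and 2 repeats the 3-week stagger.

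Section 7.4.2 (Safety Monitoring Committee) times the meeting by how long the second part of the dose group must be followed: "evaluated for at least 14 days post-vaccination; such that 35 days of safety data will have accumulated for the first 4 vaccinees". Of that second part, the same sentence states: "21 days of safety data will have accumulated for the remaining 8 vaccinees". The purpose of the meeting is explicit: "The SMC will review the cumulative safety data following the first vaccination of the lower dose group to approve dose escalation".

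Two other statements bear on the missing week. Section 3.1 expects hypersensitivity within the first day and "other severe local or systemic reactions within 72 hours, and possibly up to 3 weeks post-vaccination". Section 6.5 lists, for the Day 21 visit, a history and examination that includes the injection site, vital signs, and the task "Collect Days 14 – 20 diary card".

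**The concern.** The sentence in Section 7.4.2 presents 35 and 21 days as the result of waiting at least 14 days, but waiting 14 days does not give 21 days of data for the 8. Nor can 35 and 21 occur together on one date under a 3-week stagger.

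This is the review that clears the next dose level, for formulations that Section 1.4.2 says had not been tested in humans. Someone scheduling the meeting from Section 7.4.2 would use 14 days. The SMC could then approve escalation without the third week of follow-up for two thirds of the cohort.

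That week is relevant to this adjuvant. Section 1.4.3 reports cold abscesses in 4 of 20 Montanide ISA51 recipients in one unpublished study, with onset two to four weeks after vaccination and surgical drainage in all four. That study used a different immunogen and a larger total volume, so the rate does not carry over. The onset window does show why a day-14 look could be early. Induration of Grade 2 or higher, or abscess needing drainage, in three or more volunteers of a dose cohort is stopping criterion 4 in Section 7.5.

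**Working it through.** **Inputs.** Stagger of 3 weeks = 21 days (Section 3.1 and the footnote to Tables 1 and 2). Meeting trigger of at least 14 days for the 8 (Section 7.4.2). Stated package of 35 days for the first 4 and 21 days for the 8 (Sections 3.1 and 7.4.2). Escalation floor of 3 weeks after the 8 (Section 3.1). Diary cards for Days 0–6, 7–13 and 14–20 (Section 6.5).

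**Can the stated package be reproduced?** Days for the first 4 = days for the 8 + stagger.

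- Meeting at day 14 for the 8: 14 + 21 = 35 for the first 4.
- Meeting at day 21 for the 8: 21 + 21 = 42 for the first 4.
- Stagger implied by 35 and 21: 35 − 21 = 14 days, not 21.

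So 35 fits only the 14-day trigger, and 21 fits the 3-week floor with 42 for the first 4. The stated pair is not reproduced.

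**Do the projected dates explain it?** First-dose dates in Tables 1 and 2:

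| Cohort | First-dose dates | Steps (days) |
|---|---|---|
| PpPfs25 5 µg | 5/23, 6/6, 6/20/05 (n=4, 5, 3) | 14, 14 |
| ScPvs25 5 µg | 7/11, 8/1, 8/22/05 (n=4, 4, 4) | 21, 21 |
| ScPvs25 20 µg | 9/26, 10/17/05 | 21 |
| PpPfs25 20 µg | 11/14, 12/5/05 | 21 |
| ScPvs25 80 µg | 11/14, 12/5/05 | 21 |
| PpPfs25 80 µg | 4/24, 5/15/06 | 21 |

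Only the first PpPfs25 cohort uses 14-day steps, and it was given in three groups. When its last group reaches day 21, the first 4 have 14 + 14 + 21 = 49 days. For the first ScPvs25 cohort the figure is 21 + 21 + 21 = 63 days. Neither gives 35 and 21, and both show that 42 should be written as a minimum.

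**What is missing at day 14.** The Days 14–20 card is outstanding for each of the 8 (7 vaccine, 1 placebo): 7 of 21 diary days.

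- Among the 8: 8 × 7 = 56 of 8 × 21 = 168, or 33%.
- Among the cohort of 12: 56 of 12 × 21 = 252, or 22%.
- The Day 21 clinic visit is also outstanding for all 8.

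**Room in the schedule.** Projected days from a cohort's last first dose to the next cohort's first dose:

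- PpPfs25: 6/20 to 11/14/05 = 147; 12/5/05 to 4/24/06 = 140.
- ScPvs25: 8/22 to 9/26/05 = 35; 10/17 to 11/14/05 = 28.

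The shortest gap leaves 28 − 21 = 7 days for review. If a Day 21 visit falls at the end of its ±2-day window, 28 − 23 = 5 days remain.

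**The case against.** The strongest reply is that Section 3.1 already settles the matter. It describes 21 days of data for the 8 as what the SMC reviews before escalation, and it separately bars escalation before 3 weeks. With 14 days read as a minimum, a meeting at day 21 or later satisfies every figure, because the first 4 would then have 42 days, which exceeds 35. This stands in part. It shows which number is wrong and rules out early dosing. It does not remove the 14-day trigger from the section that schedules the meeting. The floor limits when volunteers are dosed, not what the SMC must have seen when it approves. If the figures are minimums, the real trigger is day 21, and the sentence should say so.

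Four further points are fair:

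- No projected gap is shorter than 28 days, so the listed schedule never relies on day 14. The dates are labelled tentative, however.
- Day 21 has no scheduled blood draw. Waiting adds a clinical visit and a diary card, but no laboratory data for stopping criterion 5 in Section 7.5. Injection-site findings, which criterion 4 concerns, are what the visit and the card would capture.
- The investigator must keep the SMC informed of new safety information, and the stopping criteria apply throughout. Both limit harm, but neither makes approval depend on the third week being in hand.
- Stating 35 instead of 42 for the first 4 understates their follow-up and harms nobody. It is a consistency error only.

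**Conclusion.** The concern holds. The 14-day trigger in Section 7.4.2 conflicts with the 21 days of data that the same sentence and Section 3.1 say the SMC will have. The 35/21 pair cannot arise on one date from the stated 3-week stagger. The shortfall is 7 days of follow-up in 8 of 12 volunteers, or 56 of their 168 diary-days plus the Day 21 visit. That is the most that can be missing: it assumes a two-part cohort of 4 and 8 and a meeting exactly at the trigger.

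The practical harm is modest. The text permits an early SMC approval, not early dosing, and the projected dates leave at least 28 days. Part of the study was already complete at this protocol version, and the table shading that marked it is not visible here, so the number of escalation reviews still ahead cannot be stated. The threshold should still be corrected, because it governs the escalation decision and is wrong as written.

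**What to change.** In Section 7.4.2, have the SMC meet on escalation only after the last-vaccinated volunteers of the cohort have at least 21 days of follow-up, with the Day 21 visit done and the third diary card collected. In Sections 3.1 and 7.4.2, change 35 days to at least 42 days for the first 4. Writing it as a minimum also covers cohorts given in three groups.

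The cost is a wording amendment. The meeting may fall up to 7 days later than the 14-day trigger allows. The earliest escalation date under the 3-week floor is unchanged on paper, though dosing on exactly day 21 would become hard to arrange, given the ±2-day visit window and the time needed for review. The shortest projected gap still leaves 5 to 7 days for that review.

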## Stopping Criteria

If a dose of vaccine is considered unacceptably reactogenic, dose escalation and/or additional vaccinations will be suspended until reviewed by the SMC and IND sponsor (RCHSPB). The communications from the SMC will subsequently be forwarded by the investigators to the NIAID IRB and the clinical trial site IRB. All local adverse events will be routinely reviewed by the SMC prior to granting approval for dose escalation.

The following criteria will be used to define unacceptable reactogenicity of either of the malaria vaccines. PpPfs25H and ScPvs25H will be considered separately:

1. One or more volunteers experience a SAE (as defined in **Section 7.1.2** in this protocol) that is determined to be possibly, probably or definitely related to the vaccine, **OR**
2. One or more volunteers experience hypersensitivity reaction (a Grade 3 or 4 allergic reaction, as defined **Appendix H**) that is probably or definitely related to the vaccine, **OR**
3. Any severe clinical illness occurs that is not explained by a diagnosis that is unrelated to vaccination, **OR**
4. Three or more volunteers in a single dose cohort experience Grade 2 or higher injection site induration or abscess formation requiring drainage for diagnosis and treatment. A volunteer who experiences Grade 2 or higher injection site induration/abscess following the first vaccination, may not receive the final vaccination, **OR**
5. One or more volunteers in a single-dose cohort experience a Grade 3 or higher safety laboratory abnormality (see **Appendix G**), or Grade 3 systemic AE that is determined to be possibly, probably or definitely related to the vaccine, as defined in **Section 7.2.2** in this protocol.

# Data Collection and Monitoring

## Source Documentation

Complete source documentation (laboratory test reports, hospital or medical records, etc.) is required for every study subject for the entire duration of the study. Case Report Forms (CRFs) and volunteer symptom diaries will be used to record data for subjects enrolled in the study. The Investigator is responsible for the accuracy and completeness of the data reported to the IND Sponsor in the CRFs and diaries. Data reported in the CRFs derived from source documents should be consistent with source documents or the discrepancies should be explained.

## Study Documentation

Study-related documentation will be completed as required by the IRBs, the IND Sponsor and regulatory authorities. Continuing review documentation will be submitted by the Investigator to the IRBs on the anniversary date of initial review as specified by each IRB. An annual report will be submitted by the RCHSPB to the FDA on the anniversary date that the IND went into effect. These reports will provide a brief description of the progress of the investigation as outlined in 21 *Code of Federal Regulations* 312.33 and will include any revisions of the protocol.

The Investigator will maintain adequate records of the disposition of the investigational product, including dates, quantity and use by subjects. If the study is terminated, suspended or completed, final disposition of unused vaccine supplies will be determined by the Malaria Vaccine Development Branch, in conjunction with the IND Sponsor.

In addition to the study-related documentation required by the regulatory authorities, the MVDB will also submit two reports to the IND Sponsor. The first, or interim, report will be completed after the serologic data from the 5 month (20 weeks) blood draw has been compiled. This interim report, based on the serologic response that is observed 1 month after the second immunization, will serve as the basis for deciding whether to continue with future Phase 1 testing of the formulation. A final report will be submitted by the MVDB to the IND Sponsor after trial completion.

## Retention of Records

Trial-related documents will be maintained by the Investigator for a period of 2 years after final marketing approval of the vaccine, or for 2 years following the formal discontinuation of clinical development of the product. The IND Sponsor is required to inform the Investigator as to when such documents need no longer be retained. Storage of all trial-related documents will be such that confidentiality will be strictly maintained.

## Protocol Revisions

No revisions to this protocol will be permitted without documented approval from both the IND Sponsor and the IRBs that granted the original approval for the study. This does not apply to changes made to reduce discomfort or avert risk to study volunteers. Furthermore, in the event of a medical emergency, the Investigator shall perform any medical procedures that are deemed medically appropriate. The Investigator must notify the IND Sponsor of all such occurrences. Any change to the protocol will be submitted to the participating IRBs as a protocol amendment and changes not affecting risk to volunteers may be expedited, as appropriate.

## Clinical Investigator’s Brochure

Investigators will receive the current version of the Clinical Investigator’s Brochure, which comprehensively describes all the available preclinical experience with the experimental vaccine. If relevant new information becomes available during the course of the trial, the Investigators will receive a revised Investigator’s Brochure or an amendment to the current version.

## Study Monitoring

The IND Sponsor will monitor through delegated responsibility, all aspects of the study, with respect to current Good Clinical Practices (GCP), for compliance with applicable government regulations. Prior to the start of the study, the Investigator will be informed of the frequency of monitoring visits and will be given reasonable notification prior to each visit. The objectives of a monitoring visit will be to verify the prompt reporting of SAEs, to check the availability of the signed Informed Consent, GCP adherence to the protocol, and to compare CRFs and spreadsheets with source documents for completeness and accuracy. During the monitoring visit, the Investigator (and/or designee) and other study personnel should be available to discuss the study. Study documents must be available for review throughout the course of the study. The IND Sponsor will retain originals of the FDA Form 1572 and copies of other study documents as deemed necessary.

# Statistical Considerations

## General Design

The goal of this Phase 1 vaccine trial is to demonstrate safety, reactogenicity, and immunogenicity of the PpPfs25/ISA51 and ScPvs25/ISA51 malaria vaccines in human volunteers. The results from this trial will be used to determine dosing and scheduling in subsequent trials.

### Description of the Statistical Methods to Be Employed

The purpose of this trial is to estimate event rates and patterns of immune responses as well as to compare these rates and patterns in different doses of the study vaccines and to compare the response by the two vaccines. This section briefly describes the statistical methods to be used. A detailed analytic plan will fully describe the methods. The analytic plan will discuss the planned approaches to missing data. Listings will show all observed data and, if applicable, impute values and the approaches taken for imputation.

Estimates will be presented with their 95% confidence intervals. Descriptive approaches will be used to meet the protocol objectives as stated in **Section** **2.0** of this protocol. In particular, the immunologic response for each of the 72 volunteers will be presented as individual graphs,

and all adverse events will be listed. Formal statistical tests, as outlined below, will be used to compare doses.

Statistical tests on the adverse event data will be performed without correction for multiplicity, because typically the family-wise Type I error is not bound for tests of safety. A nominal Type I error rate of 10 percent will be used. Most of the analyses of immunogenicity will be based on a longitudinal mixed model with terms for dose group for each of the 2 vaccines.

Primary Objective: To assess the safety, reactogenicity, and immunogenicity of the PpPfs25/ISA51 and ScPvs25/ISA51 malaria vaccines.

1. Summarize the frequency of immediate, systemic and local AEs.
2. Line listing of individual clinical and laboratory AEs as classified by immediate (within the first 30 minutes), systemic and local will be displayed in tabular format and stratified by dose cohort.
3. AEs will be summarized by severity and relationship to vaccine by individuals and dose cohort.
4. The proportion of volunteers with at least one local adverse event will be compared by dose cohort for each vaccine.  Formal statistical tests will assess whether the three cohorts differ with respect to these proportions, and whether there is a dose-response relationship. To see if there is a difference in adverse events between the initial vaccination and the subsequent vaccination we perform a sign test, where the response for each volunteer is the difference between the number of adverse events in the 60 days following the first vaccination and the number of adverse events in the 60 days following the second vaccination.
5. To determine the dose that generates the highest serum antibody levels to homologous antigen at Day 150 (1 month after the second immunization).

 i.   A Kruskal-Wallis test will be performed to check for any significant differences in the antibody concentrations of the three dose groups.  If that test is significant, then all three pairwise Mann-Whitney tests will be performed to see which pairs have significant differences. If the Kruskal-Wallis test is not significant then we will not perform any Mann-Whitney tests on the pairs of dose groups.  All of the tests can be performed at the 0.05 level and they will retain a family-wise error rate of 0.05

Secondary Objective 1: To assess and compare the duration of specific antibody response to homologous Pfs25 or Pvs25 over an 18 month period.

1. Describe immunogenicity responses by vaccine and dose group, over time.
2. Individual responses will be described over time and stratified by dose cohort.
3. Antibody concentration will be measured at Days 0, 14, 30, 60, 90, 120, 134, 150, 180, 270, 360 and 556. To exploit the multiple measures of antibody within each subject, a longitudinal model will be built to describe the antibody response over time. The model will explore if there are any differences between Pfs25 and Pvs25 and explore dose effects.

Secondary Objective 2: Measure the effect of boosting at 4 months on antibody units.

1. Using difference in antibody level from Day 0 to Day 150 as the response, exact Jonckheere-Terpstra tests will be performed to determine if there is a dose response. Using the same response, exact stratified Wilcoxon rank sum tests, stratified on dose level, will be performed to determine if there are differences between the dose groups. If feasible, similar tests may be done using the longitudinal model described above.
2. In addition, the increase in the levels of antibody between Day 120 and Day 150 will be estimated and compared.
3. Waning will be assessed by comparing levels of antibody at Days 180, 270, 360 and 556 with the level at Day 150.

The following tertiary objectives are for information only:

Tertiary Objective 1: To measure the ability of the vaccine induced antibody to significantly reduce or block oocyst development in the mosquito as measured by the membrane feeding assay for both Pvs25 and Pfs25.

1. Graphs will display growth inhibition (the ability of the antibody to significantly reduce or block oocyst development) expressed as a percent of inhibition comparing test sera to pre-immune sera.
2. Depending on the distribution of the data, parametric or non-parametric methods will be used to compare inhibition as a function of dose, and serotype.

Tertiary Objective 2: To determine the relationship between antibody levels and degree of in vitro oocyst development.

Non-linear regression will be used to model growth inhibition and the ELISA value giving 50% growth inhibition will be estimated.

Should the need arise for terminating the study early, the investigative team will discuss with the SMC the reason for termination and determine which study questions can be addressed in an unbiased manner with the available data. The available data will be analyzed and interpreted in light of early termination. Deviations from the statistical plan will be reported in the study report.

